## Abstract

**Introduction:**

Despite cooling, adverse outcomes are seen in up to half of the surviving infants after neonatal encephalopathy. A number of novel adjunct drug therapies with cooling have been shown to be highly neuroprotective in animal studies, and are currently awaiting clinical translation. Rigorous evaluation of these therapies in phase II trials using surrogate MR biomarkers may speed up their bench to bedside translation. A recent systematic review of single-centre studies has suggested that MR spectroscopy biomarkers offer the best promise; however, the prognostic accuracy of these biomarkers in cooled encephalopathic babies in a multicentre setting using different MR scan makers is not known.

**Methods and analysis:**

The MR scanners (3 T; Philips, Siemens, GE) in all the participating sites will be harmonised using phantom experiments and healthy adult volunteers before the start of the study. We will then recruit 180 encephalopathic infants treated with whole body cooling from the participating centres. MRI and spectroscopy will be performed within 2 weeks of birth. Neurodevelopmental outcomes will be assessed at 18–24 months of age. Agreement between MR cerebral biomarkers and neurodevelopmental outcome will be reported. The sample size is calculated using the ‘rule of 10’, generally used to calculate the sample size requirements for developing prognostic models. Considering 9 parameters, we require 9×10 adverse events, which suggest that a total sample size of 180 is required.

**Ethics and dissemination:**

Human Research Ethics Committee approvals have been received from Brent Research Ethics Committee (London), and from Imperial College London (Sponsor). We will submit the results of the study to relevant journals and offer national and international presentations.

**Trial registration number:**

Clinical Trials.gov Number: NCT01309711.

Strengths and limitations of this studyFirst and largest multicentre prospective study examining the prognostic accuracy of cerebral MR biomarkers in neonatal encephalopathy.Robust optimisation, harmonisation and quality assurance of MR biomarkers.All the three major makers of MR scanners (Phillips, Siemens and GE) included.Only centres with access to 3 T MR scanners are included.

## Background

Neonatal encephalopathy occurs in approximately 1–2 per 1000 live births in high-income countries.^1–4^ The incidence in low-income and middle-income countries is much higher.^5^ Often, neonatal encephalopathy occurs unexpectedly following an otherwise uneventful pregnancy. Before the widespread implementation of the therapeutic hypothermia, 20–25% of the affected infants died in the first few days after birth, and up to 75% of the survivors developed significant lifelong disabilities^3^
^6^ resulting in a substantial burden for the individual, their family and society.^7^

In the past 5 years, three major clinical trials of whole body or selective head cooling therapy^8–10^ showed significant reduction in death (risk ratio (RR)=0.8; 95% CI 0.7 to 0.9; p=0.005) and improvement in survival with normal neurological outcome (RR=1.5; 95% CI 1.2 to 1.9; p<0.001), after neonatal encephalopathy.^11^ The protective effect of therapeutic hypothermia persists into early childhood.^12^ Unfortunately, up to 50% of surviving infants still have adverse outcomes.^13^

For these reasons, there has been a renewed interest in other potential neuroprotectants, or adjunctive therapies, most of which have shown promising results in a preclinical stage or in pilot studies.^14^
^15^

Unfortunately, evaluating clinical efficacy of these therapies is extremely challenging for a number of reasons. First, the sample sizes for an adequately powered clinical trial of an adjunct therapy will be exceedingly high. Second, the effects on long-term outcome are likely to be more subtle and may require several years of follow-up for adequate evaluation. Finally, the intervention and the outcome measures of these neuroprotectants are likely to be highly heterogeneous (eg, different protocols, dosage and timing of the intervention) unlike the three major cooling trials, thus reducing the chances of robust meta-analysis.

MR biomarkers of injury severity have the potential to overcome many of these challenging impediments to progress. In the past decade, such MR biomarkers have enhanced our ability to identify, assess the onset and quantify the features of brain injury soon after birth.^16^ These modalities may be valuable as surrogate outcome measures of the treatment effects of adjunct neuroprotective therapies.

While conventional and diffusion-weighted neonatal MRI is currently the main modality used for the assessment of injury and prediction of outcome after neonatal encephalopathy, it is considered subjective and requires considerable time and experience for interpretation. Measurements of basal ganglia or thalamic metabolites by proton MR spectroscopy (MRS), in particular the ratio of lactate/*N*-acetylaspartate (Lac/NAA), have been shown in meta-analyses to be the most accurate cerebral MR biomarkers for predicting medium-term adverse neurological outcome currently available.^16^ Unfortunately, these data come from a very few, small single-centre studies, using a variety of MR sequences on 1.5 T MR scanners,^17–19^ and their applicability over a wider range of centres is not known. There is very little information available on the use of these MRS biomarkers on babies who have received rescue hypothermic neuroprotective therapy and in general have lesser degrees of injury than in earlier cohorts; additionally, there is a lack of data at 3 T, which is expected to be the standard platform for neonatal neuroimaging in the next decade.

Metabolite peak area ratios are affected by pathophysiological changes in both NAA and Lac, which follow very different time courses and which can be variably and independently affected by neuroprotective therapies and intercentre scanner differences.^20^ Hence, despite the good reported prediction of outcome with metabolite ratios, absolute quantification of [NAA], even though technically more challenging to estimate than metabolite peak area ratios, may offer several advantages. NAA is the second most abundant amino acid in the nervous system, and is almost exclusively neuronal. Therefore, it has been used as a surrogate index of neuronal survival. NAA concentrations measured by ^1^H MRS are theoretically absolute, reproducible,^21^ should not vary with scanner magnetic field strength, investigatory centre^20^ and correlate well with NAA concentrations measured by high performance liquid chromatography.^22^
^23^ Therefore, it is considered an ideal biomarker.

Smaller single-centre studies have also shown good correlation of reduced whole brain fractional anisotropy (FA; analysed by Tract Based Spatial Statistics—TBSS) with adverse outcomes at 2 years.^24^
^25^ TBSS is an automated observer-independent method of aligning FA images from multiple subjects to make non-biased assessments of localised changes in the major white matter tracts,^25^ and therefore is a useful tool for evaluating treatment efficiencies of neuroprotective therapies on diffusion tensor-based biomarkers.

The current study aims to harmonise the acquisition, and to qualify the use of novel quantitative cerebral MRI and MRS biomarkers for accurate prognostication of medium-term adverse outcomes in term and near term infants after neonatal encephalopathy, across several tertiary neonatal centres in the UK, and worldwide.

## Methods and design

This is a prospective multicountry observational study, which will be conducted in three phases.

*Phase A*: MRS phantoms will be prepared (expected life span 2 years) and scanned in 3 T MR scanners at the participating centres. The intercentre variability of metabolite ratios and concentrations will be examined and any effects will be investigated.

*Phase B*: Five healthy adult volunteers will be scanned at each site. Adult volunteers should be of sound health, between 20 and 45 years of age, and not pregnant at the time of scans. The intercentre variability of metabolite measurements will be examined and any effects will be investigated further.

*Phase C*: Infants with neonatal encephalopathy of presumed hypoxic-ischaemic origin and born at term and who have had rescue hypothermic neuroprotection will be recruited. The index tests (cerebral MR biomarkers) and neurological outcome at 18–24 months of age will be performed independently, and masked to each other.

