#### TBSS analysis

Whole-brain white matter FA with TBSS will be analysed using the Functional MRI of the Brain Software Library (FSL, V.4.1)^31^ and the Diffusion Tensor Imaging ToolKit (DTI-TK, V.2.3.1).^32^ Diffusion-weighted data will be corrected for motion and eddy current distortion, segmented to exclude extracerebral tissue, and used to reconstruct the diffusion tensor volume, with FSL. The diffusion tensor volumes from all the participants will be spatially normalised with an optimised pipeline in DTI-TK, prior to TBSS analysis.^33^ An FA threshold (>0.10) will be required to identify the major white matter tracts but to exclude peripheral tracts. TBSS will be used to assess the relationship between FA and outcome. The presence of group-wise FA differences with p<0.05, corrected for multiple comparisons using threshold-free cluster enhancement,^34^ will be considered statistically significant.

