### Outcomes

The primary outcome is to examine the accuracy of quantitative cerebral MR biomarkers for predicting adverse 18–24-month neurodevelopmental outcome in infants who had neonatal encephalopathy treated with therapeutic hypothermia, in a multicentre setting.

The secondary outcomes are the intercentre variability of proton MRS measurements and the incremental benefits of quantitative MR biomarkers for predicting adverse outcomes when compared with conventional MR assessment and bedside assessments and investigations such as the Apgar score at 1, 5 and 10 min; umbilical cord pH; base deficit and Lac or blood gas pH; base deficit; Lac within 1 h of birth; abnormal aEEG (voltage criteria: upper margin <10 µV, lower margin <5 µV) at 48 h; neurological examination at discharge.

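### Harmonisation is claimed for MR biomarkers generally, but the stated intercentre checks and variability outcome cover proton MRS only, although white matter FA from three scanner makers is pooled as a predictor and in TBSS

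*Protocol article*

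**What the plan says.** **The claim is general.** The abstract (Methods and analysis) states: "The MR scanners (3 T; Philips, Siemens, GE) in all the participating sites will be harmonised using phantom experiments and healthy adult volunteers". The Background gives the aim: "The current study aims to harmonise the acquisition, and to qualify the use of novel quantitative cerebral MRI and MRS biomarkers". The strengths box lists "Robust optimisation, harmonisation and quality assurance of MR biomarkers".

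**The specified checks are about spectroscopy.** Under Methods and design:
- Phase A: "MRS phantoms will be prepared (expected life span 2 years) and scanned in 3 T MR scanners at the participating centres". The comparison follows: "The intercentre variability of metabolite ratios and concentrations will be examined and any effects will be investigated".
- Phase B, five healthy adults per site: "The intercentre variability of metabolite measurements will be examined and any effects will be investigated further".

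Under Outcomes: "The secondary outcomes are the intercentre variability of proton MRS measurements", followed by the incremental value of the quantitative biomarkers.

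**FA is one of the biomarkers under study.** The sample size and data analysis section lists white matter FA as a continuous predictor beside [NAA] and Lac/NAA. The TBSS analysis section normalises the tensor volumes of all participants together and sets a significance rule: "The presence of group-wise FA differences with p<0.05", corrected by threshold-free cluster enhancement (TFCE). The processing steps named are for motion, eddy currents, removal of extracerebral tissue and spatial alignment. The MRI section provides taskcards at each site and gives typical DTI parameters for a Philips scanner.

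**The concern.** The primary question is how accurate quantitative MR biomarkers are in a multicentre setting. The Background cites only smaller single-centre studies in support of FA. It names intercentre scanner differences as a problem for metabolite ratios and argues that [NAA] should not vary by centre; it makes no such argument for FA. FA is therefore the biomarker whose agreement across makers is least supported in the article, and the one for which no agreement check is stated.

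Two consequences are possible, and they differ in seriousness. If scanners give systematically different FA values but similar infants, the offset acts as noise and FA looks weaker than it is within any one scanner. If the adverse rate also differs between scanners, part of the scanner difference can appear as an FA-outcome association, or cancel a real one. Without an FA variability result, a reader of the final report could not tell a weak marker from an unharmonised one.

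**Working it through.** **Aim and procedure side by side**

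| Element | Scope stated |
|---|---|
| Abstract, aim, strengths box | MR scanners; MRI and MRS biomarkers |
| Phase A | MRS phantoms; metabolite ratios and concentrations |
| Phase B | Metabolite measurements in five adults per site |
| Secondary outcome on variability | Proton MRS |
| Risk model | [NAA], Lac/NAA, white matter FA, aEEG, clinical examination |
| TBSS | FA, all participants |

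None of the three variability statements names FA or DTI.

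**The plan's own figure.** N = parameters × 10 / event rate = 9 × 10 / 0.50 = 180, which reproduces.

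**Illustrative size.** The article gives no FA offset and no outcome rate by scanner, so both are assumed. Set-up: N = 180, three scanner groups of 60, FA offsets of −s, 0 and +s in units of the within-scanner SD, with s = 0.5 or 1.0.

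*(a) Equal adverse rates (50% in each group).* Let δ be the true within-scanner FA difference in SD (lower FA in adverse cases). The AUC within a scanner is Φ(δ/√2). When all infants are pooled, the scanner offsets of a random adverse/non-adverse pair differ by 0 with probability 3/9, by +s or −s with 2/9 each, and by +2s or −2s with 1/9 each. So

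AUC = (3/9)Φ(δ/√2) + (2/9)[Φ((δ+s)/√2) + Φ((δ−s)/√2)] + (1/9)[Φ((δ+2s)/√2) + Φ((δ−2s)/√2)].

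| δ | s = 0 | s = 0.5 | s = 1.0 | Loss |
|---|---|---|---|---|
| 0.5 | 0.638 | 0.628 | 0.606 | 0.010 to 0.032 |
| 0.8 | 0.714 | 0.699 | 0.667 | 0.015 to 0.047 |

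Simulation at δ = 0.8 gave 0.711, 0.700 and 0.666.

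*(b) Adverse rates that differ by scanner, no true FA effect.* The expected spurious difference in mean FA is D, and V is the variance of FA within an outcome group. The standard error is √(V × 4/180), taking 90 infants per outcome group. For rates 65/50/35%, the mean offset is (−0.65s + 0.35s)/1.5 = −0.2s in adverse cases and +0.2s in the others, so D = 0.4s and V = 1 + s²(1/1.5 − 0.04).
- s = 0.5: D = 0.20, SE = √(1.157 × 4/180) = 0.160, D/SE = 1.25; rejection at two-sided 5% about 24%.
- s = 1.0: D = 0.40, SE = 0.190, D/SE = 2.10; rejection about 56%.

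Simulated rejection of a two-group t test (4,000 runs per cell):

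| Adverse rates by scanner | s = 0.5 | s = 1.0 | With scanner indicators |
|---|---|---|---|
| 50/50/50% | 5% | 5% | 5% |
| 60/50/40% | 13% | 29% | 5% |
| 65/50/35% | 23% | 55% | 4 to 5% |

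A marker with no value shows a pooled AUC of 0.54 to 0.56 at 60/50/40% and 0.55 to 0.59 at 65/50/35%.

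*(c) Opposite ordering.* With rates 35/50/65% against the same offsets, a marker with a within-scanner AUC of 0.64 (δ = 0.5) falls to 0.58 (s = 0.5) or 0.52 (s = 1.0).

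Parts (b) and (c) concern one comparison or one marker. They simulate neither the TFCE-corrected voxelwise test nor the cross-validated multivariable model.

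**The case against.** Three stronger readings are tempting, and the article does not support them.

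*That harmonisation itself is limited to spectroscopy.* It is not. The aim covers acquisition of MRI and MRS biomarkers, and the taskcards cover the MR sequences, DTI among them. Phase B says only that adults will be scanned, so DTI may already be acquired. What is limited to spectroscopy is the stated comparison between centres and the variability outcome. Taskcards set a sequence; they do not show that the resulting FA values agree.

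*That TBSS will be run without adjustment for scanner.* That would be an inference from silence in a short summary. Nuisance covariates are commonly left to a full protocol or analysis plan, neither of which is shown. The point does not rest on this.

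*That scanner differences will pass as outcome differences.* This needs adverse rates that differ by scanner and line up with the FA offset. Such variation is plausible in a multicountry study but nowhere stated. With similar case mix, the pooled AUC, scanner noise included, is a fair answer to the multicentre question, and some attenuation is a legitimate result.

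Giving priority to MRS is also defensible, since the article presents it as the most promising modality. What stands is that the article chooses the scope of its checks and of its secondary outcome explicitly, and that this scope is narrower than its claim and than the biomarkers it will analyse.

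**Conclusion.** The concern holds as a gap between claim and procedure: harmonisation and quality assurance are claimed for MR biomarkers generally, while the stated intercentre checks and the variability outcome leave out FA. As written, the study will not report whether FA agrees across the three makers.

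The firm consequence is modest. Under assumed offsets of 0.5 to 1.0 SD and equal outcome rates, FA loses about 0.01 to 0.05 of AUC, and the false-positive rate stays near 5%. The more serious consequence, a created or hidden association, is conditional on outcome rates that differ by scanner. Its size then depends heavily on how far they differ: 13 to 29% false positives at 60/50/40%, and 23 to 55% at 65/50/35%. Because neither the offsets nor the rates come from the article, these figures show what could happen, not what is expected. The change is worth making because it is cheap and bears directly on the primary question.

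**What to change.** 1. Under Outcomes, extend the intercentre-variability secondary outcome from proton MRS to white matter FA. Use the Phase B DTI where it is acquired; if it is not, it means one more sequence in a session already planned.
2. In the TBSS analysis section, state scanner as a nuisance covariate in the group comparison.
3. In the data analysis section, report for FA a scanner-stratified AUC, in which each adverse case is compared only with non-adverse cases from the same scanner and the results are pooled, beside the overall AUC. A clear difference between the two would show how much scanner contributes.

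**Cost.** Items 2 and 3 are wording and a few degrees of freedom; item 1 may lengthen the volunteer scans slightly. Separate per-scanner estimates would be imprecise (about 60 infants each if the makers share equally), which is why the pooled within-scanner AUC is preferred. Five adults per site is also few: if different adults are scanned at each site, which the article does not say, the difference between two site means has a standard error of √(2/5) = 0.63 of the between-adult SD. The Phase B result should therefore be reported with its uncertainty.

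The logistic model and N = 180 are unchanged. Adding two maker indicators to that model is not proposed here: by the article's own rule it would need 11 × 10 / 0.50 = 220 infants.

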### MRI protocol

#### Acquisition

MRI will be performed between 4 and 14 days after birth (ie, after completion of therapeutic hypothermia) in all infants, following informed parental consent. Existing MR scanning protocols will be followed in the individual centres with regard to sedation and monitoring.

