#### Conventional MRI score

Each image will be reported systematically by an experienced neonatal neurologist blinded to the clinical history but not gestational age and age at scan. Each scan will be assessed for anatomy, established injury, atrophy, haemorrhage and ventriculomegaly. Based on the scoring system developed by Rutherford *et al*,^30^ brain tissue injury will be scored from 0 to 3 for basal ganglia/thalami, white matter and cortex (0=normal, 1=mild signal abnormality, 2=moderate signal abnormality, 3=severe signal abnormality) and the posterior limb of the internal capsule scored from 0 to 2, as normal, equivocal or abnormal. The presence of focal hemispheric lesions and their site will also be noted.

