### Neurodevelopmental outcome

A standardised, validated and scorable neurological examination will be performed;^35^ the presence and type of cerebral palsy determined according to Gorter *et al*^36^ and severity classified using the Gross Motor Function Classification System (GMFCS). Neurodevelopmental outcome will be assessed using the Bayley Scales of Infant Development (BSID-III), by trained and certified examiners. Vision and audiometric evaluations^37^ will be collected alongside anthropometric data (weight, height and head circumference) as part of the follow-up evaluations. Infants will be tracked and undergo follow-up at network centres with evaluations at 18–24 months.

Outcome will be assessed according to the neurological examination score; the GMFCS level; and the cognitive, language and motor composite scores. These variables provide quantitative data that can be compared with MR measures.

Severe disability will be defined as any one of the following: Bayley III, both cognitive and language composite scores <70, GMFCS level 3–5, hearing impairment requiring hearing aids or blindness. Moderate disability will be defined as both cognitive and language composite scores between 70 and 84 and one or more of the following: GMFCS level 2, hearing impairment with no amplification or a persistent seizure disorder.

The outcomes will also be assessed by categorisation of these scores and by including mortality as an outcome. Adverse outcome will be defined as death or, in survivors, moderate or severe disability.

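### The masking does not reach deaths after redirection of care, which count as adverse; MR accuracy may be inflated, so mode of death should be recorded and two sensitivity analyses added

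*Protocol article*

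**What the plan says.** All places are in the protocol article.

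- **Methods and design, Phase C:** the MR index tests and the neurological outcome at 18–24 months "will be performed independently, and masked to each other".
- **Conventional MRI score:** the person reading the scan is "blinded to the clinical history but not gestational age and age at scan". No section says whether the treating team sees the MR results.
- **Acquisition:** "MRI will be performed between 4 and 14 days after birth", that is, once cooling has ended.
- **Exclusion criteria:** a death or a withdrawal of life support is a reason for exclusion only if it occurs before 72 h of cooling is complete. Infants who cannot be scanned within 2 weeks are excluded too.
- **Background:** conventional and diffusion-weighted MRI is "currently the main modality used for the assessment of injury and prediction of outcome after neonatal encephalopathy".
- **Neurodevelopmental outcome:** "Adverse outcome will be defined as death or, in survivors, moderate or severe disability". The mode of death plays no part. The same section first describes the neurological score, the GMFCS level and the Bayley composites, of which it says "These variables provide quantitative data that can be compared with MR measures", and then adds "The outcomes will also be assessed by categorisation of these scores and by including mortality as an outcome".
- **Sample size calculation and data analysis:** the primary outcome is analysed as yes/no by logistic regression, with about 50% adverse, 90 events and 180 infants.
- **Outcomes:** a secondary aim is the incremental benefit of quantitative biomarkers over conventional MR and bedside assessments.

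**The concern.** Masking protects a judgement made by an assessor. The 18–24-month examination is such a judgement, and the examiner can be kept unaware of the scan. Death is different. The treating team can influence whether and when it happens, and nothing in the article keeps the scan from that team.

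The Exclusion criteria recognise withdrawal of life support as something that happens in this population, and the Background names MRI as the leading prognostic tool. Because an infant must be scanned to be analysed, a death counted in the accuracy analysis comes after a scan. If care is redirected partly because the MRI looks bad, the infant dies, is scored adverse, and counts as a correct prediction whatever would otherwise have happened.

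Two quantities are at stake:

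- **Absolute accuracy**, the primary aim, may be overstated. This is most direct for conventional MRI. Spectroscopy and FA are affected only if they are reported clinically or through their correlation with conventional MRI.
- **The increment over conventional MRI**, a secondary aim, may be understated if the comparator gains more than the quantitative biomarkers do.

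The Discussion proposes such biomarkers for decisions on whether a therapy proceeds to phase III, so the accuracy estimate is meant to be relied on.

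**Working it through.** **The plan's own figure.** 9 parameters × 10 events = 90 events; 90 / 0.50 = 180 infants. This reproduces exactly, and the point does not alter it.

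**Which safeguard covers which part of the endpoint**

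| Component of adverse outcome | Who determines it | Masked to MR? |
|---|---|---|
| Moderate or severe disability | Examiner at 18–24 months | Yes (Phase C) |
| Death after the scan | Course of illness and treating team | Not stated |

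**Sensitivity.** Let E be the observed adverse events, w the deaths after redirection that followed the MRI (all test-positive), and f the fraction of those w infants who would otherwise have had a favourable outcome. E = 90 is from the plan. A true sensitivity of 0.75, w and f are assumptions, because the documents give none of them.

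True events are E − f·w, of which 0.75 are test-positive. The other f·w are test-positive and newly counted as events:

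observed sensitivity = [0.75(E − f·w) + f·w] / E = 0.75 + 0.25·f·w/E

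| w | f = 0 | f = 0.2 | f = 1 |
|---|---|---|---|
| 10 | 0.750 | 0.756 | 0.778 |
| 20 | 0.750 | 0.761 | 0.806 |

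For example, w = 10 and f = 1 gives 0.75 + 0.25 × 10/90 = 0.778. The f = 1 column is a ceiling: it assumes that every redirected infant would have done well.

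**AUC, with redirection driven purely by the marker.** This used a binormal marker, 50% adverse and one million draws. The infants with the worst marker values all die after redirection and are scored adverse. The redirected share is assumed.

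| Redirected | Deaths per 180 | Observed AUC, true 0.70 | Observed AUC, true 0.80 | Observed AUC, true 0.90 | AUC without these deaths, true 0.80 |
|---|---|---|---|---|---|
| 3% | 5.4 | 0.709 | 0.803 | 0.900 | 0.790 |
| 6% | 10.8 | 0.721 | 0.808 | 0.901 | 0.782 |
| 10% | 18.0 | 0.738 | 0.816 | 0.903 | 0.771 |
| 15% | 27.0 | 0.760 | 0.829 | 0.907 | 0.759 |

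Inflation is about 0.01–0.06 at a true AUC of 0.70, 0.003–0.03 at 0.80, and under 0.01 at 0.90. A better marker leaves less room for the bias, because fewer redirected infants would have done well. At 10% redirected, the infants who would otherwise have been favourable number 3.68, 1.60 and 0.35 of 18, so f is about 0.20, 0.09 and 0.02.

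The last column shows the opposite error. Dropping these deaths takes a true 0.80 down to 0.79–0.76, because it removes infants who were mostly correctly predicted.

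**Events left in a survivor analysis.** With d post-scan deaths among the 90 events, 90 − d remain, or (90 − d)/9 per parameter. For d = 5, 10, 15 and 20 this is 85, 80, 75 and 70 events, or 9.4, 8.9, 8.3 and 7.8 per parameter.

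**The case against.** Four objections carry weight.

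- **The Phase C statement is not false.** It describes how two assessments are carried out. A reader might infer that the plan claims test and outcome are statistically independent, and that this claim fails. The sentence does not say that. What stands is narrower: the safeguard is sound for the examination but does not extend to the death component.
- **Redirection after the MRI is not documented.** No section says that it happens, how often, or that study scans are reported to clinicians. FA from TBSS depends on normalising all participants' data together, and spectroscopy is post-processed in-house, so a direct bedside influence of these measures is less likely. This is why the point is worded as a possibility.
- **Some planned analyses already leave deaths out.** A reader might infer that nothing in the plan does so. In fact the neurological score, GMFCS level and Bayley composites exist only in survivors, and they are to be compared with MR measures. Those comparisons do not address the binary accuracy or incremental-value analyses, are not presented as a check on this bias, and do not separate deaths by mode or timing.
- **An article condenses.** Death-form fields and sensitivity analyses may be in a fuller protocol or analysis plan that is not shown. That limits the point to the masking statement and endpoint, both of which the article fixes. If the fuller documents already deal with it, only confirmation is needed.

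**Conclusion.** The point holds as a conditional one. As fixed in the article, the primary endpoint counts deaths that the masking cannot protect, so MR accuracy may be inflated and the increment over conventional MRI may be understated. It does not follow that the accuracy results are self-fulfilling: that would need a rate of redirection after MRI, which the documents do not give.

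The likely size is modest. With 10 such deaths among 90 events and a true sensitivity of 0.75, observed sensitivity runs from 0.75, if all these infants would have had an adverse outcome anyway, to 0.78, if none would. The bias matters more for a weak marker than for a strong one. The effect on spectroscopy and FA through correlation with conventional MRI, and the effect on the increment, were not quantified. This is an inexpensive improvement that should be made, not an error that undermines the design.

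**What to change.** 1. State whether conventional MR, spectroscopy and FA results reach the treating team, and say that the masking covers the MR assessments and the 18–24-month examination but not deaths.
2. Record for each death whether it followed redirection of care and whether the MRI had been reported by then.
3. Keep the primary analysis as it is. Beside it, report the binary accuracy and incremental-value analyses (a) in survivors only, with moderate or severe disability as the outcome, and (b) excluding deaths after redirection of care that followed the MRI report.
4. Present (a) and (b) with the primary result as a robustness range. Neither is unbiased, since removing these deaths can push accuracy below its true value.

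The cost is one or two fields on the death form and two additional analyses with fewer events. The sample size need not change, and no change to care is proposed. The fields should be in place from the start, because mode of death may be hard to recover later.
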